#### Subgroup analyses

Several subgroup comparisons are of interest. Because of the power of the current proposal it will, however, not be possible to establish potential interaction effects or differential effects with statistical certainty. Therefore subgroup comparisons will have a hypothesis generating function. Since certain types of trauma and PTSD are more prevalent in females, non-whites, persons with low socio-economic status and in early adulthood (i.e., 18–22) [64], three more post-hoc analyses will be performed to examine the comparative effectiveness of both CBT and paroxetine in 1) men and women, 2) different age groups and 3) low and high socio-economic status.

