**Discussion:**

This study is unique for its direct comparison of the most commonly used psychological intervention (TF-CBT) and pharmacological intervention (paroxetine) on (cost-) effectiveness on the short and the long term. The anticipated results will provide relevant evidence concerning long-term effects and relapse rates and will be beneficial in reducing societal costs. It may also provide information on who may benefit most from which type of intervention. Some methodological issues will be discussed.

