### Research aims and hypotheses

The aim of the proposed study is to compare the effectiveness and cost-effectiveness of Trauma-Focused Cognitive Behavioral Therapy (TF-CBT) to paroxetine in patients with PTSD in a randomized controlled trial in terms of PTSD symptom reduction. Secondary outcome measures include general measures of psychological wellbeing (i.e. anxiety and depression), quality of life, and related costs. Furthermore, we will take into account treatment responses by gender, age, and socio-economic status (incl. ethnic and cultural background) as previous studies show that women are twice as likely as men to develop PTSD during their lifetime [2] and indicate that different psychobiological mechanisms may play a role in the development of PTSD in women compared to men [5].

Based on previous findings of the effects of both treatments on clinical symptomatology over time, we expect the TF-CBT treatment to be more effective in PTSD symptom reduction than paroxetine most prominently at long-term follow-up, i.e. several months or years after cessation of both treatments. Furthermore, we hypothesize that CBT will be cost-effective, especially related to less expected relapse rates in comparison with pharmacological treatment. We will take into account direct medical costs (health care utilization as well as to inpatient and outpatient mental health care, day-treatment and primary physician care), direct non-medical costs (travel to and from health care providers, out-of-pocket costs) and indirect costs (lost productivity due to sick leave).

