### Self-report assessments

*Basic demographic variables*, i.e. birth date, sex, marital status, number of children, origin of parents, highest level of education, profession, number of working hours will be assessed.

*Trimbos/iMTA questionnaire for Costs associated with Psychiatric Illness (TiC-P)* is used to document resource utilization to estimate direct (i.e. medical consumption) and indirect costs (e.g. work absenteeism) associated with psychiatric illness [49]. Volumes of resource utilization will be valued by unit costs estimated according to the Dutch guideline on (unit) costing in healthcare [50]. GP visits, medical specialist visits, physical therapists, and travelling will be valued based on the guideline prices. Psychotherapy sessions will be based on reported expenses or recommended prices from the professional associations. Medication costs will be valued by their market prices [51]. The friction cost method will be used to estimate the duration of lost productivity, age adjusted average daily wages will be used to value this duration.

*World Health Organization-Quality of Life Bref (WHOQOL)* assesses quality of life [52]. The WHOQOL is a 26-item questionnaire to measure quality of life, including physical health, psychological health, social relationships and environment. Items are scored on 5-point scales from 1 (worse outcome) to 5 (best outcome) with a total range from 4–20. The Dutch version has demonstrated good content validity, construct validity and reliability [53].

*Euroqol 6-Dimensions scale (EQ-6D)* is an easy to apply self-administered questionnaire for describing and valuing quality of life [54] and can be used to generate cross-national comparisons of health state. The first part measures five health dimensions: mobility (MO), self-care (SC), daily activities (DA), pain/discomfort (PD), mood (MD) consisting of both anxiety and depression and cognitions (CD). In the EQ-6D patients report: 0 (no problems), 1 (moderate problems), and 2 (extreme problems). The second part (EQ-VAS) is a thermometer-like scale, in which patients rate their overall wellbeing from 0 (worst imaginable overall health) to 100 (best imaginable overall health). It originated from the ED-5D [55] that is shown to be valid and frequently used to assess generic quality of life and health status [56].

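### Age is grouped and socio-economic status split in two for the exploratory subgroup analyses; a median split would lose about 36% of the information on a linear treatment-by-moderator effect

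*Protocol article*

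**What the plan says.** Subgroup analyses lists three comparisons of treatment effectiveness. The first is by sex, which is naturally binary. The other two are "2) different age groups and 3) low and high socio-economic status". The number of age groups and the cut-points are not given; socio-economic status (SES) has two levels. The same section concedes that interactions cannot be established with certainty at this sample size and gives the comparisons an exploratory role. The Abstract adds, cautiously, "It may also provide information on who may benefit most from which type of intervention".

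The raw variables are finer than the groups. Self-report assessments lists the birth date among the demographic items, and also "origin of parents, highest level of education, profession, number of working hours will be assessed". Statistical analyses uses age and SES as adjustment variables in the main models without saying that they are grouped.

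Two further wordings matter. Research aims and hypotheses speaks of "treatment responses by gender, age, and socio-economic status (incl. ethnic and cultural background", which places ethnic and cultural background inside SES. The rationale under Subgroup analyses says that trauma and PTSD are "more prevalent in females, non-whites, persons with low socio-economic status and in early adulthood (i.e., 18–22", which lists non-white patients and patients with low SES as separate items.

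**The concern.** Grouping treats patients within a group as identical on the moderator. If the difference between trauma-focused therapy and paroxetine changes steadily with age or SES, a contrast between groups estimates that gradient less precisely than a term using the actual values, and the result depends on where the cut falls. The section already admits limited power. Its remaining purpose is to suggest who might respond better to which treatment, and avoidable imprecision works against that purpose.

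A smaller matter of wording goes with this. If the parenthesis in the aims were carried into the low/high split, a difference between the two halves could not be attributed to SES rather than to ethnic or cultural background.

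**Working it through.** **Inputs from the protocol article.** 90 patients, 45 per arm, 20% attrition, effect size 0.46 for 12 CAPS points (Sample size calculation adjustment); SD 26.1 in the cognitive behavioural group (Sample size calculation). The article gives no information-loss figure and no age or SES distribution, so the distributions below are assumptions.

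**The plan's own figures.** 36/(1 − 0.20) = 45 per arm, hence 90 in total; 12/26.1 = 0.46. Both reproduce. With 20% attrition, 90 × 0.80 = 72 patients remain.

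**Formula.** With a linear treatment-by-moderator effect, the share of information kept by grouping a moderator X is the squared correlation between X and its group mean. For a normal X cut in two at tail share p, this is φ(z_p)²/[p(1 − p)]. The standard error is multiplied by 1/√(share kept).

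**Median split, normal moderator.** φ(0)²/(0.5 × 0.5) = 0.3989²/0.25 = 0.637 = 2/π. The loss is 36.3%. The standard error factor is 1/√0.637 = 1.25. The interaction is estimated as if from 90 × 0.637 = 57 patients, or 72 × 0.637 = 46 after attrition.

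**Other splits.**

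| Moderator (assumed) | Grouping | Information lost |
|---|---|---|
| Normal | 40/60 | 37.8% |
| Normal | 30/70 | 42.4% |
| Normal | 20/80 | 51.0% |
| Uniform | median split | 25% |
| Age truncated normal, 18–70, mean 38, SD 12 | median split | 33% |
| Skewed age | median split | 45% |
| Ordered scale, 3 levels | cut in two | 25–33% |
| Ordered scale, 5 equal levels | cut in two | 25–50% |
| Ordered scale, 7 equal levels | cut in two | 25–63% |
| Normal | three groups | 21% |
| Uniform | three groups | 11% |
| Truncated-normal age | three groups | 18% |
| Skewed age | three groups | 28–31% |
| All four age shapes | four groups | 6–25% |

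The rows with three or four groups assume that the groups are analysed as an ordered trend.

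**What this does to power** (normal moderator, one measurement, SD 26.1, n = 90, two-sided 5%). The standard error of the interaction slope per SD of the moderator is 2 × 26.1/√90 = 5.50. A difference D in treatment effect between the upper and lower halves corresponds to a slope b = D/(2 × 0.798). Power is Φ(b/5.50 − 1.96) with the continuous term and Φ(0.798b/5.50 − 1.96) with the split.

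- D = 12: b = 7.52; power 28% continuous, 19% split.
- D = 24: b = 15.04; power 78% continuous, 59% split.
- With 72 patients the standard error is 6.15, and the pairs become 23% and 16%, and 69% and 50%.

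**The case against.** The strongest reply is that the article already disclaims these analyses: it calls them exploratory, and even with a continuous term they would be weak. A 12-point difference in treatment effect between halves is as large as the whole planned main effect, and power for it is only 28% against 19%. The gain is substantial only at 24 points, twice the planned effect. This stands, and it keeps the point minor. It does not justify grouping, because limited power is a reason to use the values that were collected.

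Cut-points and the construction of SES are commonly left to a fuller document that is not shown. That also stands, so their absence is not criticised here. The decisions to group age and to split SES into low and high, however, are made in the text itself.

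Three stronger readings are tempting, and the article does not support them.

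- *A third or more of the trial's information is discarded.* The 36% concerns only the treatment-by-moderator term, and it needs a two-way split, a near-normal moderator and a linear gradient. For age the number of groups is open, and with three or more the loss was below a third in every case computed.
- *Patients aged 18–22 form a planned subgroup.* The words "early adulthood (i.e., 18–22" describe where trauma and PTSD are more prevalent. They are rationale, not an announced cut. No age distribution is given, so neither the number of patients in that band nor a loss can be derived.
- *The low/high split mixes ethnicity with SES.* The parenthesis "socio-economic status (incl. ethnic and cultural background" stands only in the aims. The subgroup section names the two separately and never says that ethnicity enters the split. This calls for a clarification and carries no numerical loss.

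**Conclusion.** The point holds as a minor improvement to the exploratory analyses. Grouping age and splitting SES gives up precision that the collected data could supply. The benchmark is a 36% loss of information on the interaction and a 25% larger standard error. It rests on a median split, a roughly normal moderator and a linear gradient. Other two-way splits range from about 25% to over 50%. If the treatment effect changed in a step exactly at the chosen cut, less would be lost. The comparison of the two treatments in all randomized patients is not touched.

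**What to change.** In Subgroup analyses, replace the age comparison with a continuous treatment-by-age term in the linear mixed model already planned. Report the estimated treatment difference with its confidence interval at a few ages, and check curvature with a plot or a quadratic term. Replace "low and high socio-economic status" with an ordered measure, for example the level of education already collected. If profession is also to count, keep the combined measure ordered. Grouped results can stay as descriptive display.

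Add one sentence stating that ethnic and cultural background, mentioned in the aims, is not part of the SES measure used in the subgroup analyses.

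The cost is wording only, since the variables are already collected. The small downside is that linearity becomes an assumption that must be checked. The analyses remain exploratory and underpowered and should still be described so.

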### Economic evaluation

The economic evaluation will be performed from a societal perspective, with the costs per unit improvement on the primary outcome (CAPS score) as the primary outcome measure. The appropriate type of economic evaluation is conditional on the results [65]. We hypothesize that a more effective intervention will be associated with less health care utilization as well as less burden to relatives (time costs) and absence from paid work (productivity costs). Therefore, the primary analysis in the economic evaluation will be a cost-effectiveness analysis that evaluates costs associated with an improved PTSD outcome in terms of CAPS scores. In addition, a secondary analysis will evaluate cost differences in relation to differences in quality-adjusted life years (QALYs). This cost-utility analysis, resulting in an incremental cost-effectiveness ratio expressed in costs per QALY, will be included to allow comparison with other health-related interventions or programs. With a study horizon of 18 months, no discounting will be applied.

We will differentiate between direct medical, direct non-medical and indirect costs. Direct medical costs are associated with health care utilization related to the pharmacological or psychological treatment, as well as to inpatient and outpatient mental health care, day-treatment and primary physician care. Direct non-medical costs are generated by travel to and from health care providers. Indirect costs are associated with lost productivity due to absence from paid work.

Health state utilities to estimate QALYs will be derived from an EQ-6D measurement at baseline, as well as the follow-up assessments. Utility values for EQ-6D scores will be based on UK-estimates [53]. Utility scores will be uniformly interpolated, assuming constant health state between subsequent assessments.

Robustness of the results for uncertainty in the assumptions will be evaluated in sensitivity analyses, including: Dutch health states [66] and a linear interpolation between EQ-6D measurements, varying unit costs for pertinent volumes of health care utilization (e.g. therapy costs, productivity costs). In model-based analyses using data from literature about these middle to long-term effects and costs associated with PTSD patients we will extrapolate the results to estimate the effectiveness and cost-effectiveness for both treatment options on long term (3–5 years).

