**Methods/design:**

In order to compare pharmacological treatment (paroxetine) and psychological treatment (TF-CBT) in (cost-) effectiveness on the short and the long term, we will randomize 90 patients with chronic PTSD to either paroxetine (24 weeks) or TF-CBT (10–12 weeks). We will assess symptom severity and costs before and after the intervention with the Clinician Administered PTSD Scale (CAPS), the Clinical Global Impression Scale (CGI) and the Trimbos/iMTA questionnaire for Costs associated with Psychiatric Illness (TiC-P).

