### Materials

#### Interventions

**Psychotherapy Trauma-Focused Cognitive Behavioral Therapy (TF-CBT)** Participants allocated to the TF-CBT intervention, will receive 12 weekly sessions with a certified therapist who strictly follows a clinician manual for TF-CBT. CBT will be given by therapists who have clinical experience and at least a Master’s degree in Clinical Psychology or in Medicine and should have followed the training for TF-CBT at our department, in order to properly execute the clinician manual. The therapist will receive supervision regularly (once a month) and all sessions will be tape-recorded.

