##### Pharmacotherapy paroxetine (Seroxat)

Participants allocated to the pharmacotherapy intervention will receive paroxetine (Seroxat). Treatment will be given by certified psychiatrists according to a manual that is developed and adjusted by the research staff of this study.

Pharmacotherapy will be in accordance with Dutch guidelines of pharmacotherapy for anxiety disorders [8] and the NICE guidelines for clinical excellence [9]. Paroxetine treatment will start with psycho-education and discuss paroxetine intake and possible side effects. Paroxetine treatment will be initiated at 20 mg daily for 4 weeks. After 4 weeks the study psychiatrist can increase the dosage with increments of 10 mg daily each 4 weeks up to a maximum of 60 mg daily if according to the judgement of the study psychiatrist, the patient does not respond to lower dosages and if clinically tolerated. After 24 weeks of treatment the antidepressant will be gradually discontinued (tapering off in 10 or 20 mg decrements per week). If discontinuation/withdrawal symptoms do emerge and are mild, the psychiatrist will reassure the patient that these symptoms are not uncommon after discontinuing an antidepressant and will disappear in a few days. If symptoms are severe, reintroduction of the original antidepressant and gradual tapering is required.

On each visit during treatment the psychiatrist monitors for adverse side effects, evaluates compliance with the Morisky Medication Adherence Scale [43] and documents mental health status with the Clinical Global Impression scale. All subjects will be asked to fill out the Impact of Event Scale-Revised [42]. Every session takes 20–30 minutes. The psychiatrist will be instructed not to perform any direct psychotherapeutic interventions at the visits.

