### Assessments

Assessments will take place pre-intervention (T0), 1 week post-intervention (T1) and 3, 6, 12 and 18 months at follow-up (T2-T5). Below we will describe the instruments that we will use in more detail.

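### The 18-month economic horizon has no stated origin and does not match the plan's own inputs; totals from baseline to the last visit would give paroxetine about 12 more weeks of costs and QALYs than TF-CBT

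*Protocol article*

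**What the plan says.** **Horizon.** The Economic evaluation section says "With a study horizon of 18 months, no discounting will be applied" and gives no starting point.

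**What is accumulated.** The same section says "Health state utilities to estimate QALYs will be derived from an EQ-6D measurement at baseline, as well as the follow-up assessments". It also counts the cost of the two study treatments among direct medical costs. The primary economic result is cost per unit of CAPS improvement; cost per QALY is secondary.

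**Visit clock.** The Assessments section places visits at "1 week post-intervention (T1) and 3, 6, 12 and 18 months at follow-up (T2-T5". Study design calls these visits post-treatment, and the sample size adjustment places the 18-month comparison after treatment as well.

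**Treatment length.** The abstract gives "either paroxetine (24 weeks) or TF-CBT (10–12 weeks". The Interventions section says TF-CBT patients "will receive 12 weekly sessions with a certified therapist". The paroxetine section says "After 24 weeks of treatment the antidepressant will be gradually discontinued (tapering off in 10 or 20 mg decrements per week". Strengths and limitations acknowledges about 24 weeks against about 12 weekly sessions. The initial sample size calculation, however, speaks of treatment periods of 12 weeks without separating the arms.

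**Sensitivity analyses.** Those listed cover Dutch health-state values, linear interpolation between utility measurements, and unit costs. None concerns the length of the observation window.

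**The concern.** Costs and QALYs are sums over time. If the arms are summed over windows of different length, a difference appears even when the treatments have identical effects and identical weekly costs. Here the inputs run from baseline to a last visit that is timed from the end of treatment, and treatment is planned to be about twice as long in one arm. The single figure of 18 months hides this, because it is the post-treatment follow-up and not the span from baseline to T5.

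Both economic results use these sums. If the window is left undefined, it could also be chosen after the data are seen, and that choice could move the cost-effectiveness result.

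**Working it through.** **Inputs**
- TF-CBT: 12 weeks (Interventions), or 10 as the lower end in the abstract.
- Paroxetine: 24 weeks (abstract and paroxetine section).
- T5: 18 months after the end of treatment (Study design; Sample size calculation adjustment; Assessments).
- Conversion: 365.25 / 12 / 7 = 4.348 weeks per month, so 18 months = 78.3 weeks and 12 months = 52.2 weeks.

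**Does 18 months reproduce as baseline to T5?** Window = treatment weeks + 78.3.

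| Arm | Weeks | Months |
|---|---|---|
| TF-CBT, 12 weeks | 12 + 78.3 = 90.3 | 20.8 |
| TF-CBT, 10 weeks | 10 + 78.3 = 88.3 | 20.3 |
| Paroxetine, 24 weeks | 24 + 78.3 = 102.3 | 23.5 |

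It does not reproduce in either arm. The figure of 18 months fits only the stretch after treatment.

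**Excess accrual for paroxetine**
- Against 12 weeks of TF-CBT: 24 − 12 = 12 weeks; 12 / 90.3 = 13.3%.
- Against 10 weeks: 24 − 10 = 14 weeks; 14 / 88.3 = 15.9%.

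The percentage is also the inflation in total cost if weekly costs are equal in both arms, which is an assumption.

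**QALYs from the excess alone.** Extra QALY = utility × weeks × 7 / 365.25. The document gives no mean utility; the range 0.6 to 0.8 is assumed.
- 12 weeks: 0.230 year × 0.6 = 0.138; × 0.8 = 0.184.
- 14 weeks: 0.268 year × 0.6 = 0.161; × 0.8 = 0.215.

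**Possible readings of the horizon**
1. *Baseline to T5.* This fits the utility and cost inputs, but the windows are unequal and neither is 18 months.
2. *Eighteen months from the end of treatment.* The windows are equal, but the treatment phase lies before them, although the section uses baseline utility and counts treatment costs.
3. *Eighteen months from randomisation.* The windows are equal at 78.3 weeks. They reach 78.3 − 12 = 66.3 weeks (15.2 months) after TF-CBT and 78.3 − 24 = 54.3 weeks (12.5 months) after paroxetine. T5 then lies outside the horizon in both arms.

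No reading agrees with every statement in the document.

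**The case against.** The strongest reply is the third reading. A common 18-month window from randomisation is workable: week 78 falls just after paroxetine T4 (24 + 52.2 = week 76) and between TF-CBT T4 (12 + 52.2 = week 64) and T5 (week 90). The gap then disappears, and the document never expressly says that sums run to T5. This stands as far as it goes, so the excess is a consequence of summing to T5 and not a declared plan. But the document does not state that reading, mentions no truncation, and names the follow-up assessments as the utility source without excepting T5.

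The visit clock is also not watertight. The initial sample size text implies 12 weeks of treatment in both arms, which would equalise the windows. That conflicts with the 24 weeks given elsewhere, so it is a further point to reconcile and does not settle the matter.

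Two stronger inferences are tempting and fail:
- *An excess of 18 to 20 weeks.* With dosing "up to a maximum of 60 mg daily" and steps of 10 mg per week, the longest taper is 60 / 10 = 6 weeks, so 24 + 6 − 12 = 18, or 20 against a 10-week course. This needs a follow-up clock that starts after the taper, which is nowhere stated. It also needs every patient to be at the maximum dose, whereas treatment starts at 20 mg and rises only for non-response.
- *The treatment costs will be omitted.* The section expressly counts them. The second reading creates a conflict of wording and is no evidence of a plan to leave them out.

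**Conclusion.** The point holds. The stated horizon lacks an origin and disagrees with the plan's own inputs. Summed from baseline to T5, paroxetine would accrue about 12 more weeks than TF-CBT, about 13% more time, or 14 weeks against a 10-week course. This rests on the visit clock starting when the 24 or 12 weeks end. The corresponding 0.14 to 0.18 QALY (12 weeks) depends on the assumed utility range.

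A reader might infer that the error must favour TF-CBT. The document does not support that in general. In cost per CAPS point the outcome is a score that does not accumulate, so only costs are affected, and extra time adds cost to paroxetine. In cost per QALY paroxetine gains both costs and QALYs, so the net direction is not fixed.

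The discounting sentence is secondary: it relies on an 18-month horizon, while the inputs span about 20.8 and 23.5 months.

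**What to change.** - State where the horizon starts and ends. Accumulate all costs, including those of treatment, and all QALYs over one common window from randomisation in both arms.
- A practical choice is to about week 90, the T5 visit after a 12-week TF-CBT course. For paroxetine, interpolate between T4 (about week 76) and T5 (about week 102) using actual visit dates. Say how this works under the base-case rule that holds utility flat between visits and under the linear sensitivity analysis.
- Replace the 18-month figure with that window and recheck the no-discounting sentence against it.
- Reconcile the 12-week treatment periods in the initial sample size calculation with the 24 weeks of paroxetine in the abstract, the paroxetine section and the limitations. State whether the follow-up clock starts before or after the taper.

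**Cost.** Only the analysis wording changes and no visit is added, provided actual visit dates are recorded, which the document does not say. About 12 weeks of late paroxetine data (weeks 90 to 102) drop out of the base case, and about 14 of the 26 weeks between paroxetine T4 and T5 rest on interpolation. After a 10-week TF-CBT course T5 falls near week 88, so about 2 weeks would need a carry-forward rule or a slightly earlier cut-off.

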### Study design

The study is designed as a randomized controlled trial comparing TF-CBT and paroxetine treatment. The randomization and allocation procedure will be performed by a researcher who has no further role in data collection. The study design was set up with one pre-treatment assessment and four post-treatment assessments (at 1 week, 6 months, 12 months and 18 months) but before starting data-collection the authors added an assessment at 3 months as well (see Figure 1). All assessments will be performed by research workers blinded for the allocated treatment. The study will be performed at the department of psychiatry of the Academic Medical Center (AMC) in Amsterdam. Patients will be recruited over the course of 3 years, starting November 2009.

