### Procedure

All patients referred to the outpatient psychiatric clinic at the AMC will receive a diagnostic medical intake procedure, in which psychiatric and medical history are examined. In case PTSD diagnosis is suspected, the intake procedure will consist of standardized diagnostic measures for PTSD and other DSM-IV diagnoses (CAPS and M.I.N.I.-Plus). If PTSD is confirmed and all inclusion criteria are met, the patient will be requested to participate in the study. After giving informed consent, a baseline assessment (T0) will be performed. This assessment will consist of self-reported symptoms of PTSD, depression and anxiety and questionnaires on quality of life and costs. Subsequently, patients will be randomized to either TF-CBT or paroxetine treatment. One week after treatment, another assessment will be done (T1), consisting of the same questionnaires. At 3 months (T2), 6 months (T3), 12 months (T4) and 18 months (T5) assessments will be repeated. Figure 1 shows a flowchart of the study. Table 1 explores an overview on all instruments being assessed.

**Table 1 T1:** Overview of instruments per assessment time point

	***Baseline (T0)***	***Treatment***	***1-week follow-up (T1)***	***3-month follow-up (T2)***	***6-month follow-up (T3)***	***12-month follow-up (T4)***	***18-month follow-up (T5)***

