### Strengths and limitations

A particular strength of the study is that it is unique in comparing a pharmacological treatment with psychological treatments on the short and the long term. Its sample size is sufficient to differentiate the treatment in effectiveness and cost-effectiveness over the short and the long term, where at present only studies are available that did not take into account long-term effects [11,28].

Some limitations may affect the trial that need to be considered. Firstly, even though we aimed to reduce different influencing factors between pharmacological factors and psychological factors, this is rather difficult as the nature of the two treatments differs. Regarding this difference, the two treatments vary in duration as well as in number and length of the sessions, with pharmacological treatment approximately 24 weeks and psychological treatment consisting of approximately 12 weekly sessions. As we already outlined previously, the length of pharmacological treatment is very essential with possible high relapse rates during short-term treatments [29,31]. Despite these differences, we strived for similarity within the protocols as much as possible; both protocols consist of comparable psycho-education as well as a relapse prevention session. Furthermore, questionnaires will be performed in the same order in both treatment protocols. Other differences intertwined in the nature of both treatments should not be eliminated since the comparison of both treatments should be based on conditions that reflect routine clinical practice in this pragmatic effectiveness trial.

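### Holding utility constant between visits in the QALY base case can under-credit paroxetine, whose first EQ-6D after baseline comes about 12 weeks later than in the TF-CBT arm

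*Protocol article*

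**What the plan says.** All references are to the protocol article.

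- **Rule.** Economic evaluation sets the base case: "Utility scores will be uniformly interpolated, assuming constant health state between subsequent assessments". Among the sensitivity analyses it lists "Dutch health states [66] and a linear interpolation between EQ-6D measurements".
- **Measurements.** The same section states: "Health state utilities to estimate QALYs will be derived from an EQ-6D measurement at baseline, as well as the follow-up assessments". In Table 1 the treatment column for EQ-6D is empty.
- **Timing.** Procedure places the first repeat after the end of therapy: "One week after treatment, another assessment will be done (T1), consisting of the same questionnaires". Study design describes the later visits as post-treatment as well, so they are not fixed from randomisation.
- **Treatment length.** Strengths and limitations describes the arms as unequal, "with pharmacological treatment approximately 24 weeks and psychological treatment consisting of approximately 12 weekly sessions". The abstract gives 24 weeks against 10 to 12.
- **Role and horizon.** Cost per unit of CAPS improvement is the primary economic analysis, and cost per QALY is secondary. The horizon is 18 months; its starting point is not given.

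**The concern.** Baseline and T1 bracket the whole treatment phase. That gap is about 25 weeks for paroxetine and 11 to 13 weeks for TF-CBT. If the baseline utility is held until T1, a patient who improves on paroxetine in the first months is credited from about week 25. A patient who improves in the same way on TF-CBT is credited from about week 13. Two arms with the same recovery would then show different QALYs because of when they were measured.

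At stake is the cost per QALY, which the protocol includes so that the result can be compared with other health interventions. The error runs towards TF-CBT, the arm that the protocol expects to be cost-effective. The protocol acknowledges the unequal treatment lengths, but the economic section does not take up what they do to the QALYs.

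**Working it through.** The protocol states no QALY figure, so there is none to reproduce. The check compares the difference that each rule would compute with the true difference.

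**Inputs from the protocol.** Treatment lasts 24 weeks (paroxetine) or 12 weeks (TF-CBT; 10 is also tried). T1 is one week later, so week 25 or week 13. T2 is 3 months after treatment, so week 25 for TF-CBT.

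**Assumptions.** Both arms gain the same utility g (0.10 to 0.20 for illustration). The horizon is 78 weeks from randomisation in both arms. The gain lasts once reached.

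**Weeks of full gain credited up to week 78** (divide by 52 and multiply by g for QALYs):

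| Recovery path | Rule | TF-CBT | Paroxetine | Error in the difference |
|---|---|---|---|---|
| A. Both reach g by week 12, rising evenly | Truth | 78 − 6 = 72 | 72 | – |
| | Held forward | 78 − 13 = 65 | 78 − 25 = 53 | −12/52 = −0.231g |
| | Linear | 78 − 6.5 = 71.5 | 78 − 12.5 = 65.5 | −6/52 = −0.115g |
| B. Both rise evenly to g at week 25 | Truth | 65.5 | 65.5 | – |
| | Held forward | 0.52 × 12 + 53 = 59.24 | 53 | −6.24/52 = −0.120g |
| | Linear | 65.5 | 65.5 | 0 |
| C. Each arm rises evenly to its own T1 | Truth | 71.5 | 65.5 | – (true difference −6) |
| | Held forward | 65 | 53 | −12 + 6 = −6, so −0.115g |
| | Linear | 71.5 | 65.5 | 0 |

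In B the TF-CBT value at week 13 is 13/25 = 0.52 of the gain, and it is held to T2 at week 25.

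**Size of the held-forward error.** Path A gives 0.231 × 0.10 = 0.023 to 0.231 × 0.20 = 0.046 QALY. Paths B and C give about 0.012 to 0.024. A gain held for the full 18 months is worth 78/52 = 1.5g, so path A loses 0.231/1.5, about 15% of that, and path C about 8%.

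**TF-CBT of 10 weeks** (T1 at week 11, gain complete by week 10): (25 − 11)/52 = 0.269g, or 0.027 to 0.054 QALY. Linear interpolation gives 7/52 = 0.135g, or 0.013 to 0.027.

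**Other directions of carry.** Under path A, using the midpoint of the two values gives −0.115g, and carrying T1 backward gives 0. Carrying backward is not neutral in general. Under path B it credits paroxetine 25 weeks and TF-CBT 0.52 × 13 + 12 = 18.76 weeks up to week 25, an error of +6.24/52 = +0.12g in favour of paroxetine.

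**Horizon.** If each arm were instead summed to its own T5, the paroxetine window would be 12 weeks longer and its raw total higher. With an assumed baseline utility of 0.60 and g = 0.10, path A then gives a computed difference of 0.1385 against a true 0.1615. The shortfall is again 0.023.

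**Relapse.** If paroxetine utility falls evenly by d between T1 and T2 (12 weeks), holding forward over-credits it by 6/52 = 0.115d. For a fall spread over a 26-week gap such as T3 to T4, it is 13/52 = 0.25d.

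**The case against.** Five points can be made for the plan as written.

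1. **The direction of carry is not in the text.** This stands. Holding each value until the next visit is the natural reading of a constant state, but it is an inference. The error is therefore conditional, and the missing direction is itself something to settle.
2. **Full recovery by week 12 is demanding for an SSRI.** The Background reports that more than half of the 41% who had not responded at 12 weeks did so with at least 24 weeks of treatment. This also stands, and it is why the slower paths are shown. They bring the error to about half, not to zero. The same figures imply that about 59% had responded by week 12.
3. **A reader might infer that the whole cost-utility comparison is biased towards TF-CBT.** The documents do not support that. The protocol anticipates relapse after paroxetine, and the forward rule is slow to register a fall, which credits paroxetine too much. The net error over 18 months cannot be derived from the protocol.
4. **Linear interpolation is already planned.** True, so readers would see the dependence on the rule. But it is not the base case, and under early recovery it leaves half the error. Visit timing is the remaining cause.
5. **The Sample size calculation section speaks of 12-week treatment periods.** With equal periods the effect would vanish. That wording conflicts with the 24 weeks in the abstract, the paroxetine section and the limitations, and the passages must be reconciled. The working uses the 24 weeks given there. If T1 is set after the paroxetine taper, the gap is longer still.

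A reader might also want to object to UK utility values as the base case. Dutch values are already a sensitivity analysis, and nothing shows that the choice favours one arm.

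**Conclusion.** The point holds in conditional form. If each utility is held to the next visit, the base-case rule understates paroxetine relative to TF-CBT by about 0.12 to 0.23 times the utility gain. That is 0.012 to 0.046 QALY for assumed gains of 0.10 to 0.20, with TF-CBT at 12 weeks and before any offset from relapse. The upper end requires the full gain by week 12 in both arms; the lower end applies when utility rises evenly.

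Linear interpolation did no worse than the forward rule on any of the three recovery paths: it halved the error on one and was exact on the other two. It should not be read as a cure, because no utility is measured at common times during treatment. The primary economic analysis, cost per CAPS improvement, does not use this rule and is not affected. The change is worth making, but it does not threaten the trial's main conclusions.

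**What to change.** In Economic evaluation:

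- Make linear interpolation (area under the curve) the base case, using the actual EQ-6D dates counted from randomisation, over a horizon that starts and ends at the same time in both arms.
- Keep the constant-state rule as the sensitivity analysis, and state which value is carried across each interval.
- Add a sentence acknowledging that unequal timing of T1 can leave an error of up to about 0.115 times the utility gain against paroxetine (0.135 if TF-CBT lasts 10 weeks) when recovery is early, to be borne in mind when the cost per QALY is interpreted.

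Both interpolation analyses are already planned, so this takes a few sentences and no new data. Measuring EQ-6D at common times from randomisation would deal with the remainder, but it means extra assessments and is not needed for this change.
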